## **5.3 Safety, Toxicity, and Adverse Events**

### **5.3.1 Dose-limiting Toxicity**

DLTs will be tracked using the NCI CTC (Version 3.0) and our own Clinical Neurologic Change (CNC) criteria. CNC will be defined as a decrease in the Mini-mental Status Examination (MMSE) of  $\geq 6$  points, a decrease in KPS of  $\geq 30$  points, or the development of a new focal neurologic deficit. A DLT will be defined as any irreversible CNC, irreversible Grade 3 toxicity, any Grade 4 toxicity, or any life-threatening event not attributable to a concomitant medication, co-morbid event, or disease progression that has been documented histologically. If biopsy cannot be obtained, any new radiographic or clinical changes, as defined above, will be considered a DLT. Also as defined above, any life-threatening event, even if considered a Grade 3 toxicity, will still be considered a DLT even if reversible. CNC and Grade 3 toxicities will be declared irreversible if they cannot be reversed within 2 months of their onset.

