### **6.2.2 Prior to Initial Leukapheresis**

After patients have been enrolled, and before leukapheresis, a ProTRAK form will be submitted to the Cancer Center Protocol office. All enrolled patients will then undergo a leukapheresis for baseline immunological monitoring. Prior to leukapheresis, patients will have blood samples taken for the following tests as required by the Duke Apheresis Center: OP8 (Lab Code 1004500) and  $\beta$ -HCG (Lab Code 1800440). Total estimated blood volume required for these evaluations is 10 cc. For patients without sufficient venous access for leukapheresis, a temporary intravenous catheter may be inserted. To prevent the development of hypocalcemia from the citrate used for leukapheresis, all patients will be given oral Tums, 2 tablets, b.i.d for 2 days prior to the leukapheresis procedure. Patients who have lowered levels of calcium will be treated per Apheresis lab standard protocols under the direction of [name], M.D. All leukaphereses will be 2 to 4-hours long, and it is estimated that 1.5 to 3 times the blood volume (~10-12 L) will be processed during all leukaphereses.

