### **6.2.4 During and After Immunizations**

- Clinical evaluations with each vaccine or leukapheresis will include a general physical, neurologic, and ophthalmologic examination, KPS, and MMSE.
- Radiographic evaluations consisting of a contrast enhanced brain CT or MRI scan will be obtained every 8  $\pm$  4 weeks.
- Blood will be obtained for T4/T8 ratio (Lab Code 2500202), ABC (Lab Code 2010200) with manual differential (Lab Code 2000640), serum for PEPvIII-KLH ELISA ([name] Lab), and 10 yellow ACD (9 mL), 3 red (9 mL), and 1 purple (3 mL) tubes for Immunologic Monitoring *prior* to vaccination #1 and with each vaccination after vaccination #3. Blood will also be obtained for

sub-clinical autoimmunity prior to vaccine # 1 and every 4 months after vaccine # 3. Estimated volume of blood for these tests is 120 cc.

- During TMZ cycles, ABC (Lab Code 2010200) with manual differential (Lab Code 2000640) will be monitored at the time of vaccination (day  $21 \pm 2$ ) and before the next TMZ dosing of each 4 week cycle.
- DTH testing will occur with the fourth vaccination (SOP-JHS-HDC-CL-014 “Delayed Type Hypersensitivity Testing Procedure”). Results will be read and recorded on the appropriate form (FORM-JHS-HDC-CL-014C “Delayed Type Hypersensitivity Testing Form”)  $48 \pm 24$  hours later. An additional leukapheresis will be required for any patients who have a positive DTH skin test for PEPvIII for immunologic monitoring.

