### **9.2.10     Temozolomide**

TMZ has been well tolerated by both adults and children with the most common toxicity being mild myelosuppression. Other, less likely, potential toxicities include nausea and vomiting, constipation, headache, alopecia, rash, burning sensation of skin, esophagitis, pain, diarrhea, lethargy, hepatotoxicity, anorexia, fatigue and hyperglycemia. Hypersensitivity reactions have not yet been noted with TMZ. As in the case with many anti-cancer drugs, TMZ may be carcinogenic. Rats given TMZ have developed breast cancer. The significance of this finding for human is not presently known. TMZ therapy will be followed but given as standard of care. If toxicities occur, the Principle investigator and primary physician will titrate therapy based on standard clinical guidelines as outlined above.

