### **9.2.11 Daclizumab**

In trials of renal transplantation, the overall incidence of infectious episodes, including viral infections, fungal infections, bacteremia and septicemia, and pneumonia was not higher in the daclizumab-treated patients than the placebo-treated patients. There was, however, a slight increase in wound infections, specifically, with daclizumab. Addition of daclizumab also did not increase the number of post-transplant lymphomas up to three years post-transplant. No difference in abnormal hematologic or chemical laboratory test results were seen between groups treated with placebo or daclizumab with the exception of fasting blood glucose which was likely related to corticosteroids or diabetes. While low titers of anti-idiotypic antibodies to daclizumab were detected in adult patients treated with the drug, no antibodies that affected efficacy, safety, serum daclizumab levels or any other clinically relevant parameter examined were detected.

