## 11 STUDY FLOW SHEET

| Appointment                                                | Time and Range                | Curran Rating
EGFRvIII screen
HIV Screen
Hepatitis | Physical,
Ophthalmologic,
and Neurologic
Exam
MMSE
KPS | MRI  | EGFRvIII PCR
EGFRv III ELISA
Blood for
Autoimmunity and
Immunologic
monitoring  | DTH  | ABC 
T4/T8 | CMP 
β-HCG  |
|------------------------------------------------------------|-------------------------------|-------------------------------------------------------------|-----------------------------------------------------------------------|-------------------|-------------------------------------------------------------------------------------------------------------|-------------------|----------------------------|------------------------------------------|
| Screening and Pre-enrollment                               | Week ≤4 from leukapheresis    | X                                                           |                                                                       |                   |                                                                                                             |                   | X                          |                                          |
| Pre-Immunization Leukapheresis                             | Prior to Temozolomide         |                                                             | X                                                                     | X    | X                                                                                                           | X                 | X                          | X                                        |
| Radiation with Temozolomide                                | 6 ± 2 weeks duration          |                                                             |                                                                       |                   |                                                                                                             |                   | X                          |                                          |

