 All ABC should be obtained with manual differential counts. ABC should always be obtained with T4/T8 counts. These should be obtained at least weekly during concurrent external beam radiation and temozolomide, immediately before and within 1h after ALT, and then subsequently on day of vaccine and immediately prior to next temozolomide cycle.

 Comprehensive Metabolic Panel (CMP)

 Obtained BEFORE each leukapheresis only. B-HCG only required for females.

 MRI here is just post-operative eligibility MRI

 Post-radiation MRI will be done a minimum of 10 days after completing radiation therapy.

 Cohort 2 will receive daclizumab at same dose with vaccine # 1, # 3, and on day 21 ± 2 for 3 TMZ cycles.

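### No renal, electrolyte, bilirubin or glucose test is scheduled after daclizumab or saline in patients DTH-negative to PEPvIII, and no fixed chemistry draw falls in the 2-week window that governs further enrollment

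*Protocol*

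**What the plan says.** The last column of the flow sheet in Protocol section 11 is headed "CMP 24 β-HCG 25". Footnote 24 only spells out the abbreviation, "Comprehensive Metabolic Panel (CMP". Footnote 25, attached to the pregnancy test, reads "Obtained BEFORE each leukapheresis only. B-HCG only required for females". The column is marked at the leukapheresis before temozolomide (TMZ) and at the visit triggered by a positive DTH test to PEPvIII, and nowhere else.

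The text agrees. Section 6.2.2 ties "OP8 (Lab Code 1004500") and the pregnancy test to leukapheresis. Section 6.2.1 lists only blood counts and T4/T8 during TMZ. Section 6.2.4 lists counts, T4/T8, ELISA serum and immunology tubes with vaccination, and for the TMZ cycles says "During TMZ cycles, ABC (Lab Code 2010200) with manual differential (Lab Code 2000640) will be monitored at the time of vaccination".

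The only other chemistry is the autoimmunity panel (sections 6.1.1 and 8.11, flow-sheet footnote 21). It includes ALT and AST for every patient, before vaccine #1 and at 4-month intervals after vaccine #3.

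On the decision side, section 5.3.1 states "A DLT will be defined as any irreversible CNC, irreversible Grade 3 toxicity, any Grade 4 toxicity" and adds life-threatening events. A Grade 3 toxicity becomes irreversible if it is not reversed within 2 months of onset. Sections 5.3.2 and 10.2 open the next cohort if no toxicity is seen within 2 weeks.

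**The concern.** The safety of daclizumab is the first secondary objective, and the DLT and halting rules rest on graded toxicity. Part of that grading is biochemical and often silent. The protocol itself lists "hepatotoxicity, anorexia, fatigue and hyperglycemia" among the possible toxicities of TMZ, and hepatitis among the autoimmune manifestations seen in related trials. The TMZ tables in section 5.1.3 also turn on graded non-hematologic toxicity. If chemistry is not drawn after dosing, an asymptomatic Grade 4 or irreversible Grade 3 change has no scheduled test to reveal it, date its onset or show its reversal. At stake are the completeness of the DLT count and the decision to open each cohort.

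**Working it through.** No stated figure needs reproducing. The check sets the schedule against the decision rules and then does the date arithmetic.

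**1. Marks in the flow sheet**

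| Row | ABC and T4/T8 | CMP |
|---|---|---|
| Screening | X | none |
| Leukapheresis before TMZ | X | X |
| RT with TMZ; initial TMZ cycle | X | none |
| Immunizations #1, #2, #3 | X | none |
| TMZ cycles; immunizations #4 and #5 | X | none |
| Positive DTH to PEPvIII | X | X |
| Progression | X | none |

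Scheduled CMPs after vaccine #1 in a DTH-negative patient: 0. The protocol does not list the analytes of the CMP. I assume the usual content, which includes creatinine, electrolytes, bilirubin and glucose.

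**2. First ALT/AST after dosing**

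Inputs from section 11: vaccine #1 with daclizumab or saline on day 21 ± 2, and vaccine #3 on day 49 ± 7. Four months = 4 × 365.25/12 = 121.75 days.
- Nominal: 49 + 121.75 = 170.75, about day 171. Interval from dose: 170.75 − 21 = 149.75, about 150 days.
- Shortest interval: (42 + 121.75) − 23 = 140.75, about 141 days.
- Longest interval: (56 + 121.75) − 19 = 158.75, about 159 days.

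The flow sheet also marks the combined autoimmunity and immunology column at immunization #4. If that mark is read as including the autoimmunity panel, and the next TMZ cycle starts on day 49 to 63 (an assumption), the draw falls on day 49 + 20 = 69 to day 63 + 20 = 83.

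**3. Against the protocol's own windows**
- Two weeks, counted from vaccine #1 (the starting point is not stated, so this is an assumption): 21 + 14 = day 35, range 33 to 37. Both readings of the ALT/AST schedule fall later. A DTH-triggered CMP has no fixed day, and the first flow-sheet DTH mark after vaccine #1 is at immunization #3, day 42 at the earliest.
- Two months for irreversibility, if onset is at dosing: 21 + 60.9 = about day 82. On the 4-month reading, a silent Grade 3 rise in ALT could begin, last more than 2 months and resolve before day 171. On the immunization #4 reading, the first draw comes close to the 2-month mark.

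**4. Cohort #2**

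Assume the three TMZ-cycle doses follow vaccine #3. With cycles starting on day 49 to 63, the last daclizumab dose is on day 49 + 20 + 56 = 125 to day 63 + 20 + 56 = 139. On the 4-month reading, all five doses precede the first ALT/AST after dosing.

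**5. Illustration of the effect on halting**

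The protocol gives neither a DLT rate p nor the share s of DLTs that is detected, so both are assumptions. For two or more DLTs among six patients (section 10.2), P = 1 − (1 − ps)^6 − 6ps(1 − ps)^5.

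| p | s = 1 | s = 0.5 |
|---|---|---|
| 0.10 | 0.114 | 0.033 |
| 0.20 | 0.345 | 0.114 |
| 0.33 | 0.642 | 0.259 |

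This shows the direction of the effect only. Silent chemistry toxicity may be a small part of all DLTs, which would put s close to 1.

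**The case against.** Several stronger conclusions are tempting, and the protocol does not support them.

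- *Hepatic toxicity goes unmonitored.* ALT and AST are scheduled for every patient, whatever the DTH result. They are sparse and late, not absent.
- *The DLT and halting rules are blind to chemistry.* Section 5.3 is not limited to scheduled tests, and section 5.4 counts any laboratory abnormality as an adverse event. Every vaccine visit includes a physical, neurologic and ophthalmologic examination. Symptomatic events and abnormalities on prompted tests are captured. TMZ is also given as standard of care, which may bring further chemistry. The protocol neither requires this nor says how much.
- *The footnote restricts the CMP to leukapheresis.* Its marker is on the pregnancy test. The evidence for the CMP is the pattern of marks and the silence of section 6.2.
- *Daclizumab has a known glucose signal.* Section 9.2.11 reports no laboratory differences from placebo in transplant trials, "with the exception of fasting blood glucose which was likely related to corticosteroids or diabetes". Read in full, this is mild reassurance.
- *Ascertainment is biased by arm.* A repeat CMP follows only a positive DTH, and daclizumab is hypothesized to enhance immune responses, so a difference is conceivable. No figure supports it. Both cohort 1 arms share one schedule, and toxicity is evaluated independently in each arm.

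It can also be said that this is a design choice that leaves the TReg primary endpoint untouched. That is true. What stands is that asymptomatic laboratory toxicity, which the rules count, has almost no scheduled means of detection.

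**Conclusion.** The point holds in a limited form. In a patient DTH-negative to PEPvIII, no renal, electrolyte, bilirubin or glucose test is scheduled after daclizumab or saline. The next scheduled ALT/AST after the pre-vaccine #1 draw is about 150 days (141 to 159) after the first dose, or about day 69 to 83 on the alternative reading. On either reading, no fixed chemistry draw falls inside the 2-week window. Scheduled testing may therefore miss asymptomatic Grade 4 or irreversible Grade 3 laboratory toxicity that sections 5.3 and 10.2 treat as dose-limiting. The gap is common to all arms and is not specific to daclizumab. How many events would be missed cannot be derived from the protocol, because off-schedule chemistry is not described. The dates rest on the nominal visit days, on the 2 weeks running from vaccine #1 and, for cohort #2 and immunization #4, on the assumed cycle starts.

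**What to change.** Reconcile section 11 and section 6.2.4 with sections 5.3 and 10.2. Mark the CMP at the vaccine visits where the flow sheet already has an ABC: before dosing at vaccine #1, then at #2, #3 and each later vaccine, identically in all arms. Tabulate graded chemistry toxicity by arm. The draw at vaccine #1 also supplies a CMP baseline after RT and the first TMZ cycle; the present one precedes both. State in footnote 21 whether the immunization #4 mark includes the autoimmunity panel.

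One limit remains. Vaccine #2 is nominally on day 35, the last day of the 2-week window, and may fall as late as day 42. Section 10.2 should therefore say whether that result is expected before the cohort decision.

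The cost is one extra tube and assay at each existing draw. No visit is added, and no dose or treatment rule changes.
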